# 9.0 Analysis Plan:

This is a phase II, four-group, placebo-controlled, randomized clinical trial. Approximately 28 subjects will be treated in each group. Volunteers will either receive two 15 µg treatments separated by two weeks, one 30 µg and one placebo treatment separated by two weeks, two 30 µg treatments separated by two weeks, or two placebo treatments separated by two weeks. In the immediate post-treatment period, outcomes are pre-specified local and systemic reactions, general adverse event rates, and immune responses assessed by antibody measurements.

Forty-one (± 3) days after the first treatment, subjects who remain eligible are challenged and then followed for an additional week regarding evidence of illness (by several alternative definitions), and also concerning virologic outcomes.

All analyses will be done with SAS, version 8.2 or later, primarily PROC UNIVARIATE, FREQ, LOGISTIC (for logistic regression with challenge data), and GENMOD (SAS PROC GENMOD implements the repeated measures regression model of Zeger and Liang [48].) Chi-square tests in PROC FREQ are exact. In this phase II trial which will not be used to provide definitive evidence of efficacy or safety, p-values of 0.05 or less for two-sided statistical tests will be considered significant and multiple comparison corrections will not be used (although the rather large number of significance tests – at least as regards safety -makes it likely that the type I error rate will be somewhat elevated.

Simple methods will be used to impute missing data. For binary outcomes, such as the presence/absence of an adverse event, alternative imputations will assume the event did, and did not, occur and the results of these contrary assumptions will be compared. For continuous outcomes, such as antibody titers, last-value-carried-forward will be used except that two consecutive missing values will not be imputed.

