### 9.2.1 Power and Detectable Effect Size:

In regard to the immediate post-treatment component of the study design, we address the following two questions: What must be the chance of a given reactogenicity event/finding or adverse event in a single subject for there to be a high likelihood (probability 0.80) of a few occurrences in 28(any one treatment group) and 84 (all active treatment) subjects? Secondly, comparing three cross-over groups in the same period, what must be the relative risk of a reactogenicity event/finding or adverse event for the groups to differ significantly in risk? Exact calculations are based on the binomial distribution.

| Chance of an event in a single subject so that there is an 80% chance of at least the given number of events in 28 or 84 subjects | | | |
| --- | --- | --- | --- |
|  |  1 |  2 |  3 |
| n = 28 | 0.056 | 0.103 | 0.146 |
| n = 84 | 0.019 | 0.035 | 0.050 |

Thus, events that occur with probability of about 6% and 2% in a single subject imply an 80% chance of seeing at least one event in, respectively, any given treatment group and all actively-treatment subjects. This phase II study is not intended to be powered to detect rare events.

Turning to comparison of any two cross-over groups, 28 subjects in each, in the same period, we compute the relative risk (RR) that gives 80% power, type I error 5%, to detect RR  1.

| Chance of an adverse event in a placebo vaccinee so that a given risk-ratio yields a significant effect (80% power, 5% type I error) | | | |
| --- | --- | --- | --- |
| relative risk | 5-fold | 3-fold | 2-fold |
| placebo rate | 0.074 | 0.178 | 0.381 |

Thus, for a five-fold relative risk of an adverse event or reactogenicity event, active-to-placebo, to be detectable (with good power), the chances of an adverse event in the placebo group must be 0.074. With a lower adverse event rate among placebo subjects, there would not be good power to detect even a five-fold increase in risk However, for the most frequent reactogenicity events observed with intranasal proteosome-influenza vaccine, mild rhinorrhea and nasal congestion, prior experience indicates that placebo rates will range from 0.2 – 0.3. Thus, there will be adequate power to detect between two- and three-fold increases in risk in active product recipients.

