### 9.2.2 Immediate Complaints, Vaccine Reactogenicity Complaints, and Standardized Ear, Nose, and Throat Exams:

Immediate complaint data derived from 30 minute post-dose questionnaires will be tabulated for each treatment group by categories of complaints and by severity. Vaccine reactogenicity data derived from memory aids and physician examinations will be similarly tabulated by treatment group, categories of complaints or findings, severity, and duration.

Comparison of graded severities for local and systemic reactogenicity: Comparing one group with another during a period (the cross-over design has two periods), these are two-sample, cross-sectional comparisons of binary, ordinal, or continuous data. Comparing a group with itself between periods, these are paired, repeated measures data. Two-sample, cross-sectional comparisons are based on Fisher’s exact and Cochran-Mantel-Haenszel tests for binary and ordinal outcomes, respectively. Student’s-t and Wilcoxon tests are used for continuous outcomes. These methods permit statistical tests to address the following topics:

- 1. comparison of active and placebo after test article dose 1
  2. comparison of active and placebo after test article dose 2, with and without testing for the impact of, and adjustment for, outcomes after dose 1
  3. comparison of active and placebo in successive test article doses
  4. comparison of placebo in successive test article doses
  5. comparison of change from active to active with change from placebo to placebo

Items c. and d. are paired comparisons, which may be performed by McNemar tests or, more flexibly, by General Estimating Equation (GEE) models with a binary or continuous outcome. Items b. and e. are tests of interaction: dose 1 by dose 2 in item b., and period by vaccine in item e. and also accessible by GEE models.

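### The relative-risk table in section 9.2.1 claims 80% power at placebo rates where the planned Fisher's exact test gives 69% to 76%

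*Protocol*

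**What the plan says.** Protocol section 9.2.1 has two tables. The first gives the per-subject event probability needed for an 80% chance of seeing at least one, two or three events. The second concerns between-group comparison. It is introduced with "Turning to comparison of any two cross-over groups, 28 subjects in each, in the same period" and "we compute the relative risk (RR) that gives 80% power, type I error 5" percent. Its rows read "relative risk | 5-fold | 3-fold | 2-fold" and "placebo rate | 0.074 | 0.178 | 0.381". The text below it repeats the first entry: for a five-fold risk to be detectable, "the chances of an adverse event in the placebo group must be 0.074". The section describes its calculations as exact and binomial-based but does not name the test behind the second table.

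The test and the level are fixed elsewhere. Section 9.2.2 states: "Two-sample, cross-sectional comparisons are based on Fisher’s exact and Cochran-Mantel-Haenszel tests for binary and ordinal outcomes, respectively". Section 9.2.3 allows adverse events to be handled like the binary reactogenicity outcomes. Section 9.0 sets the criterion: "p-values of 0.05 or less for two-sided statistical tests will be considered significant". It also rules out multiplicity correction, so the 5% level applies to each comparison.

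Section 9.2.1 closes by expecting placebo rates of 0.2 to 0.3 for the commonest nasal complaints and concludes that increases of between two- and three-fold can be detected with adequate power.

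**The concern.** A power statement holds only for the test that will be run. Fisher's exact test is conservative with groups of 28, most of all when the placebo rate is low. A table computed for a less conservative test will therefore promise more than the analysis delivers. The tabled rates look too low to give 80% power with Fisher's test.

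Safety and tolerability is the trial's first objective, and this table is the only stated sensitivity for its between-group safety comparisons. If it is optimistic, a reader could take a non-significant difference as firmer evidence of no large increase in risk than the design supports. In the 5-fold column the chance of missing the effect is about 31%, where the table implies 20%.

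**Working it through.** **Inputs.** 28 per group, 80% power and 5% type I error (9.2.1); two-sided p ≤ 0.05 with no multiplicity correction (9.0); Fisher's exact test (9.2.2); placebo rates p₀ of 0.074, 0.178 and 0.381 with RR of 5, 3 and 2 (9.2.1). The implied active rates RR × p₀ are 0.370, 0.534 and 0.762.

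**Step 1: the first table in 9.2.1.** For at least one event, solve 1 − (1 − p)ⁿ = 0.80, so p = 1 − 0.2^(1/n). This gives 0.056 for n = 28 and 0.019 for n = 84, as printed. The remaining entries come from the binomial tail: 0.103 and 0.147 for n = 28 (the protocol prints 0.146 for the second), and 0.035 and 0.050 for n = 84. That table reproduces apart from one last digit, so the problem is confined to the second table.

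**Step 2: power with the planned test.** For x placebo and y active events with s = x + y, the conditional probability of a table is C(28,x)·C(28,y)/C(56,s). The two-sided Fisher p-value sums these probabilities over all tables with the same s that are no more probable than the one observed. Then

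Power = Σₓ Σᵧ b(x; 28, p₀) · b(y; 28, RR·p₀) · 1{p-value ≤ 0.05},

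where b is the binomial probability and the sums run over all 29 × 29 outcomes.

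| RR | p₀ stated | Active rate | Fisher power | Shortfall from 80% (points) | p₀ needed for 80% | RR needed at stated p₀ |
|---|---|---|---|---|---|---|
| 5 | 0.074 | 0.370 | 68.5% | 11.5 | 0.087 | 5.6 |
| 3 | 0.178 | 0.534 | 74.4% | 5.6 | 0.193 | 3.14 |
| 2 | 0.381 | 0.762 | 76.0% | 4.0 | 0.393 | 2.04 |

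**Step 3: whether another method explains the row.** Power at the stated rates, n = 28 per group:

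| Method | RR 5 | RR 3 | RR 2 |
|---|---|---|---|
| Uncorrected chi-square, enumerated | 0.795 | 0.821 | 0.834 |
| Fisher mid-p | 0.784 | 0.803 | 0.827 |
| Fisher, one-sided | 0.785 | 0.837 | 0.845 |
| Yates-corrected chi-square, enumerated | 0.685 | 0.722 | 0.748 |
| Pooled normal approximation | 0.775 | 0.812 | 0.841 |
| Arcsine approximation | 0.808 | 0.819 | 0.842 |
| Continuity-corrected normal | 0.659 | 0.721 | 0.760 |

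None of these, nor the likelihood-ratio, Wald, log-odds-ratio or log-relative-risk versions, lies within 2 points of 80% in all three columns. The uncorrected chi-square is among the closest, but its own 80% rates are 0.0747, 0.171 and 0.368, not the printed ones.

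**Step 4: the expected placebo rates of 0.2 to 0.3.** With Fisher's test, the ratio detectable with 80% power is 2.94 at 0.2, 2.60 at 0.25 and 2.35 at 0.3. A three-fold risk at 0.2 has 82% power. A doubling has 28% power at 0.2 and 51% at 0.3.

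**The case against.** The strongest reply accepts the arithmetic and disputes its weight.

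- The closing conclusion survives: ratios of 2.94 and 2.35 both lie between two and three. This stands. The sentence needs figures attached, because it can be read as covering every ratio in that range, but it is not false.
- Low power for a doubling at 0.2 to 0.3 is no discovery, since the table itself places a 2-fold risk at a placebo rate of 0.381. This also stands.
- The shift in the table's own terms is small: 0.013, 0.015 and 0.012 in the placebo rate. This stands for the 3- and 2-fold columns. In the 5-fold column 0.013 is about 17% of the entry (0.0125/0.074, from the unrounded 0.0865), and the power loss is 11.5 points.
- The protocol disclaims definitive safety evidence and power for rare events, and neither the sample size nor any decision rule rests on this table. That limits the consequence.
- The table names no test; on an uncorrected chi-square two entries are slightly conservative and the third misses by half a point. Section 9.2.3 is also permissive about adverse events. This suggests that the table was computed for a different test from the planned one, not that it was grossly miscalculated. It does not rescue the claim, because section 9.2.2 specifies Fisher's test for the binary reactogenicity comparisons and the table is offered as their sensitivity.

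**Conclusion.** The concern holds. With the test and two-sided level the protocol specifies, the three tabled placebo rates give 68.5%, 74.4% and 76.0% power, not 80%. The rates that give 80% are about 0.087, 0.193 and 0.393. The result assumes 28 evaluable subjects in each of the two groups compared, independent binomial outcomes and an unadjusted two-sided 0.05 level. Fewer evaluable subjects would lower the power further.

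The error is in the optimistic direction but its practical weight is modest. It changes no sample size, analysis or decision rule, and the broad statement about two- to three-fold increases stands once figures are attached. It should be corrected because it misstates the sensitivity of the comparison serving the first objective.

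**What to change.** In section 9.2.1:

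1. Replace the placebo-rate row with 0.087, 0.193 and 0.393, and state that it refers to the two-sided Fisher's exact test at 0.05 with 28 subjects per group.
2. Change the repeated 0.074 in the text below the table to 0.087.
3. Reword the closing sentence to say that the risk ratio detectable with 80% power is about 2.94 at a placebo rate of 0.2 and about 2.35 at 0.3.

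If a different test is intended for these comparisons, name it in section 9.2.2 and recompute the row for it, since the printed entries match none of the methods tried.

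The cost is three table entries and two sentences. Design, sample size and conduct are unchanged; the stated sensitivity becomes slightly less favourable.

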### 9.2.2 Immediate Complaints, Vaccine Reactogenicity Complaints, and Standardized Ear, Nose, and Throat Exams:

Immediate complaint data derived from 30 minute post-dose questionnaires will be tabulated for each treatment group by categories of complaints and by severity. Vaccine reactogenicity data derived from memory aids and physician examinations will be similarly tabulated by treatment group, categories of complaints or findings, severity, and duration.

Comparison of graded severities for local and systemic reactogenicity: Comparing one group with another during a period (the cross-over design has two periods), these are two-sample, cross-sectional comparisons of binary, ordinal, or continuous data. Comparing a group with itself between periods, these are paired, repeated measures data. Two-sample, cross-sectional comparisons are based on Fisher’s exact and Cochran-Mantel-Haenszel tests for binary and ordinal outcomes, respectively. Student’s-t and Wilcoxon tests are used for continuous outcomes. These methods permit statistical tests to address the following topics:

- 1. comparison of active and placebo after test article dose 1
  2. comparison of active and placebo after test article dose 2, with and without testing for the impact of, and adjustment for, outcomes after dose 1
  3. comparison of active and placebo in successive test article doses
  4. comparison of placebo in successive test article doses
  5. comparison of change from active to active with change from placebo to placebo

Items c. and d. are paired comparisons, which may be performed by McNemar tests or, more flexibly, by General Estimating Equation (GEE) models with a binary or continuous outcome. Items b. and e. are tests of interaction: dose 1 by dose 2 in item b., and period by vaccine in item e. and also accessible by GEE models.

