## 5.1 Immunization Phase:

FluINsure™ will be delivered as one of three different treatment regimens as detailed below in section 5.1.1. In addition, approximately one of every four subjects will receive a placebo control treatment regimen comprising two sequential doses of buffered saline placebo.

The study will enroll up to 112 healthy adult subjects selected for susceptibility to A/Panama/2007/99 into the immunization component.

Healthy normal subjects of both genders and 18 to 50 y.o. will be invited to give informed consent for preliminary screening phlebotomy, and then have a serum specimen obtained for baseline A/Panama/2007/99 HAI antibody testing. Screened subjects with serum reciprocal HAI titers ≤ 10 will be invited to return for a detailed explanation of the clinical trial and asked to give informed consent for participation in the trial itself. Consenting subjects will then undergo an assessment of their medical history, physical examination, ECG, and selected clinical laboratory tests to ensure eligibility according to the protocol. A nasal wash sample for measurement of secretory IgA (nasal sIgA) specific for the vaccine virus strains will be obtained during screening.

5.1.1 Treatments:

Eligible subjects will be randomized, using a gender-specific randomisation list prepared by the Sponsor, to one of four treatment groups in a ratio of approximately 1:1:1:1. The treatment groups will receive:

Treatment Group A) Two intranasal spray doses, each dose containing 15 μg of each of three hemagglutinins (HA) formulated with proteosomes. The first dose will be given on day 0 and the second given after a 14-day interval.

Treatment Group B) Two intranasal spray doses, the first containing 30 μg of each of three hemagglutinins (HA) formulated with proteosomes, and the second containing buffered saline (placebo). The first dose will be given on day 0 and the second given after a 14-day interval.

Treatment Group C) Two intranasal spray doses, each containing 30 μg of each of three hemagglutinins (HA) formulated with proteosomes. The first dose will be given on day 0 and the second given after a 14-day interval.

Treatment Group D) Two intranasal spray doses of buffered saline. The first dose will be given on day 0 and the second given after a 14-day interval.

All dose volumes will be 0.28 mL (as 0.14 mL per nostril). Each treatment group will include approximately 28 subjects.

5.1.2 Safety and Tolerability Evaluation:

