### 9.2.4 Vital Signs and Clinical Laboratory Measures:

Mean values for each measure will be plotted separately by treatment group, including ± one standard deviation. Extreme values and/or outliers will be discussed individually. For clinical laboratory measures within cross-over groups, quantitative outcomes at baseline and day 28 will be compared by paired Student’s t-tests and Wilcoxon signed rank tests. Binary outcomes will be compared by McNemar’s tests. This analysis is also vulnerable to elevated type I error.

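### Section 9 calls a parallel-group trial a cross-over, and two of its stated safety contrasts (item c of 9.2.2 and the laboratory tests of 9.2.4) make no use of the randomized placebo group

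*Protocol*

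**What the plan says.** Section 9.0 describes the design correctly: "This is a phase II, four-group, placebo-controlled, randomized clinical trial". Section 5.1.1 assigns subjects "to one of four treatment groups in a ratio of approximately 1:1:1:1", and 9.0 adds "Approximately 28 subjects will be treated in each group". Groups A and C receive active vaccine twice. Group B receives two doses, the first active "and the second containing buffered saline (placebo". The control is "Treatment Group D) Two intranasal spray doses of buffered saline". No group receives placebo first and active second.

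Section 9.2.2 nevertheless reads: "Comparing one group with another during a period (the cross-over design has two periods". Sections 9.1, 9.2.1, 9.2.4 and 9.3.8.2 also speak of cross-over groups. The third topic in the 9.2.2 list, called item c in the text below it, is "comparison of active and placebo in successive test article doses". It is described as a paired comparison, by McNemar test or GEE.

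Section 9.2.4 states: "For clinical laboratory measures within cross-over groups, quantitative outcomes at baseline and day 28 will be compared by paired" Student's t and Wilcoxon signed rank tests, with McNemar tests for binary outcomes. It also plots means with standard deviations by treatment group and discusses outliers individually. It names no test between groups. Sections 7.2.1, 7.2.2 and 7.2.4 put the baseline sample at the second screening visit (days -90 to -5) and the second sample at day 28 ± 3.

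**The concern.** A paired comparison of active with placebo is a sound treatment contrast when the order of treatments is balanced, as in a true cross-over. Here the order is fixed. Within group B, anything that differs between the first and second dose is confounded with the switch from vaccine to saline. Examples are habituation in completing the memory aid and carry-over from the first dose.

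The laboratory analysis has the same weakness. A change from screening to day 28 that affects everyone, such as assay or seasonal drift between the March screening and the June immunization given in the synopsis, appears as a change in each group. Seeing which groups reach p ≤ 0.05 is not a test of whether an active group differs from placebo.

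At stake is the first objective in section 2.0, which says that the regimens will be compared with a placebo treatment for safety and tolerability. A randomized concurrent control exists, and these two contrasts leave it out.

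**Working it through.** The protocol gives no figure that rests on these contrasts, so there is none to reproduce. The check has two parts: which comparisons use the control, and how the two contrasts behave when the vaccine has no effect.

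**Which comparisons use the control (9.2.2 list and 9.2.4)**

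| Contrast | Groups involved | Uses group D? |
|---|---|---|
| Item a: active v placebo after dose 1 | A, B, C v D | Yes |
| Item b: active v placebo after dose 2 | between groups | Yes |
| Item c: active v placebo in successive doses | B only, within subject | No |
| Item d: placebo in successive doses | D, within subject | Shows the period effect only |
| Item e: active-active change v placebo-placebo change | A, C v D | Yes |
| 9.2.4 laboratory tests | each group, within subject | No between-group test |

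Item e is the right kind of contrast, a period-by-vaccine interaction, but it covers active-to-active change only. Group B's change is therefore never set against group D's.

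**Inputs**
- n = 28 per group (5.1.1, 9.0); two-sided 0.05 without correction (9.0).
- Placebo rates of 0.2 to 0.3 for the commonest reactogenicity events (9.2.1).
- Size of any period effect or laboratory drift: not in the protocol, so assumed over a range.

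**Item c, no vaccine effect.** With independent reports and event rates p1 after dose 1 and p2 after dose 2, the discordant probabilities are p1(1 − p2) and p2(1 − p1). For 0.30 and 0.20 they are 0.30 × 0.80 = 0.24 and 0.20 × 0.70 = 0.14. The exact McNemar test is then evaluated over all outcomes for 28 pairs.

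| Rate after dose 1 → dose 2 | Exact McNemar rejects | Uncorrected McNemar rejects |
|---|---|---|
| 0.25 → 0.25 (no shift) | 2.3% | 4.2% |
| 0.25 → 0.20 | 3.5% | 6.2% |
| 0.30 → 0.20 | 7.7% | 11.9% |

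With a within-subject latent correlation of 0.5, simulation gives 8.8% (exact) and 15.8% (uncorrected) for 0.30 → 0.20.

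**The same situation with the control used.** A test of group B's change against group D's (simulated two-sample t-test on within-subject differences, latent correlation 0.5) rejects 4.6% to 4.9% of the time. This was checked at assumed shifts of 0.35, 0.45 and 0.50 down to 0.25, all larger than those above. A period effect common to both groups cancels.

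**Laboratory values, no vaccine effect.** The interval between samples runs from 28 − 3 + 5 = 30 days to 28 + 3 + 90 = 121 days. For a common drift of d SDs of the within-subject change, the paired t-test has non-centrality d√28, 27 degrees of freedom and critical value 2.052.

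| Assumed drift d | d√28 | Significant in any one group | In at least one of three active groups: 1 − (1 − p)³ |
|---|---|---|---|
| 0.2 | 1.06 | 0.175 | 0.44 |
| 0.3 | 1.59 | 0.334 | 0.70 |
| 0.5 | 2.65 | 0.723 | 0.98 |

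These are per analyte. The placebo group has the same single-group probability. A comparison of active with placebo stays at 5%, because common drift cancels.

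**The case against.** A reader might infer that any drift will be read as a vaccine effect. The protocol does not say so. It states no attribution rule, and 9.2.2 says only that the methods permit tests on the listed topics. Items a and b compare active with concurrent placebo, so group B's active dose already has a valid comparison in item a. Item d would expose a period effect, and item e removes it for the two-dose groups. This stands, and it limits the item c point to one contrast among five.

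A seasonal explanation does not suit item c, because its doses are 14 days apart. It is plausible only for the laboratory data.

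Larger false-positive rates for item c can be produced by assuming larger falls in reporting, but those would leave the 20% to 30% placebo range. The protocol documents no dose-order effect in placebo recipients.

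The cross-over label is largely a matter of wording: 9.0 states the design correctly and no cross-over estimator is specified. That is also fair.

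On laboratory data, the placebo group gets the same paired tests and plots, so a common drift could be seen. Clinically significant findings become adverse events (8.4), which may be compared between groups (9.2.3). This softens the gap but leaves continuous values without a formal comparison. The elevated type I error acknowledged in 9.2.4 does not answer the point, since a multiplicity correction would not remove a common drift.

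Finally, a between-group model could be left to an analysis plan. But the protocol does specify the laboratory tests, and those it specifies do not use the control.

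**Conclusion.** The point holds in a limited form. The cross-over wording is wrong for this design. Item c is a before-after contrast in one group with a fixed order, and nothing in the list sets group B's change against group D's. Section 9.2.4 names no test of continuous laboratory values between an active group and placebo.

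The effect on item c is modest within the protocol's own placebo range: about 8% rejection against about 2% with no shift (exact test, 28 subjects, independent reports). The laboratory effect can be large, at about 0.18, 0.33 or 0.72 per group for drifts of 0.2, 0.3 or 0.5 SD, but these drift sizes are assumptions. The documents do not show that such drift will occur or that it would be attributed to vaccine. Both are safety contrasts in a phase II trial that disclaims definitive evidence. The change is worth making because it is free and brings the tests into line with the first objective.

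**What to change.** 1. **9.2.2, item c:** compare group B's dose 1 to dose 2 change with group D's, through the group-by-period term of the GEE model already foreseen for item e. Otherwise, label item c descriptive.
2. **9.2.4:** compare day 28 laboratory values of each active group with placebo by a linear model on treatment group and baseline value. Compare normal/abnormal shifts by an exact between-group test. Keep the paired within-group results as descriptive.
3. **Section 9 and the matching synopsis text:** replace cross-over groups with treatment groups, and remove the statement that the design is a cross-over. Correct the reference in 9.2.1 to three such groups, since there are four.

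The cost is analysis wording only. No visit, sample or subject is added, and all the data are already scheduled for collection.
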